##### Daily living physical activity (DLPA)

An accelerometer (Power Walker SW 610, Japan) will quantify the absolute change in DLPA. The accelerometer records the total daily number of steps, the number of steps performed at moderate intensity (≥110 steps per minute) and the time spent during DLPA. The assessment will be performed over a period of 7 days, and the DLPA will be quantified before and after the interventions. The accelerometer automatically records the total number of steps during the 7 days, and each patient will record their amount of moderate intensity DLPA in a dairy. The accelerometer will be used to average the number of steps performed during the 5 day period (disregarding the first and last days)
[27].

##### Maximal exercise capacity

Shuttle walking test
[28] will assess exercise capacity and it will compare the absolute change in maximal exercise capacity post-intervention. Cones set up in a corridor will demarcate 10 meters, and the patients will be asked to walk around the cones at a speed pre-determined by sound signals. The sound signals indicate the moment when the patient must round the cone, and the speed increases at a rate of 0.6 km/h per minute. The total protocol consists of 12 stages, and the test can be discontinued by the individual or the therapist if the patient is unable to maintain the speed required to complete the stage (distance greater than 0.5 m from the cone). The test will be discontinued if the patient present chest pain, intolerable dyspnea, dizziness, cramps, leg pain or pallor. Patient’s heart and respiratory rates, blood pressure, dyspnea and leg fatigue will be measured before and after the test. The scale of perceived exertion
[29] will be used to measure dyspnea and leg fatigue.

##### Pulmonary function

It will be evaluated using spirometry (SensorMedics 229; SensorMedics Corp; USA) before and after the inhalation of 200 mg of salbutamol. Technical procedures of spirometry will be performed as recommended by the American Thoracic Society and European Respiratory Society
[30]. Predicted normal values will be used as proposed by Pereira et al.,
[31]. An increase of 12% and 200-mL in FEV_1_ (from baseline) will be characterized as a positive response to the bronchodilator.

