### Outcome measures

#### Primary outcome

The asthma control questionnaire (ACQ)
[22] will be used to assess asthma control. We will compare the differences between the 2 interventions in the absolute change in asthma control post-intervention. This questionnaire is validated to measure asthma control in adult patients and have been validated to Brazilian Portuguese
[23]. ACQ is a simple instrument and is easy to use that quantifies the following asthma symptoms: nocturnal and morning symptoms, limitation of daily activities, dyspnea and wheezing, and the use of medication (short-acting β_2_-agonist). Patient’s will be scored on a scale ranging from 0 to 6 (0 = without limitation and 6 = maximum limitation). The clinical score of forced expiratory volume (% of predicted, pre-bronchodilator) will be scored on similar scale. The items will be calculated, and the scores of the ACQ will be the average from 7 items between 0 (fully controlled) and 6 (severely uncontrolled). The cutoff will be adopted from previously developed studies, considering controlled (ACQ <0.75 points), not well controlled or poorly controlled asthma (ACQ > 1.5 points). A clinically effective treatment results in a 0.5 point decrease in the score after the intervention
[24].

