#### Airway inflammation

It will be quantified in collected sputum samples and exhaled fraction of nitric oxide (FE_NO_). Before the sputum collection, subjects will be advised to blow their nose and rinse their mouth with water and swallow it to reduce contamination of the sputum specimen with postnasal drip and saliva. Then, patients will inhale 400 μg of salbutamol followed by a 3% hypertonic saline solution inhaled over 15 min using an ultrasonic nebulizer with an output of 2.4 mL.min^-1^ and a mass median aerodynamic diameter of 4.5 μm as previously described
[36]. Sputum samples will be visually separated from the saliva and divided into 2 aliquots. One aliquot will be spread over a glass slide, to be fixed and stained with Diff Quick (Sigma-Aldrich, São Paulo, Brazil). The second aliquot will be treated with 0.1% of dithiothreitol (Sigma-Aldrich, USA) and stirred using a vortex mixer for total and differential cell counts. The total cell counts will be performed using a Neubauer chamber, and the cell suspension will be adjusted to 1.0 × 10^6^.mL^-1^. Differential cells counts will be classified as eosinophils, lymphocytes, neutrophils, macrophages, squamous cells, goblet cells, and ciliated cells on the basis of their morphology by a single-blinded investigator.

*FE*_*NO*_ will be measured according to the ATS/ERS guidelines (2011)
[37]. Briefly, patient’s will be asked to blow into a Mylar bag, (keeping the expiratory pressure at the mouth at 12 cm H_2_O to avoid air contamination from the nasal cavity). Exhaled air will be filtrated before being collected into the bag, and the expiratory pressure achieved by the individual will monitored by a manometer. All collected samples will be mixed 10 s before the determination of NO concentration by chemiluminescence (Sievers 280 NOA; Sievers Instruments, USA) and analyzed up to 24 h after sample collection. The equipment will be calibrated before each analysis.

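### The inhaled salbutamol dose for spirometry is given in milligrams and the dose before sputum induction in micrograms: an unexplained 500-fold difference that points to a unit error

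*Protocol article*

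**What the plan says.** The protocol article gives a numerical dose of inhaled salbutamol in two places.

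- **Secondary outcomes, Pulmonary function.** Spirometry is carried out "before and after the inhalation of 200 mg of salbutamol". A rise in FEV1 of 12% and 200 mL from baseline "will be characterized as a positive response to the bronchodilator".
- **Other notable outcomes, Airway inflammation.** Before sputum collection, "patients will inhale 400 μg of salbutamol followed by a 3% hypertonic saline solution inhaled over 15 min".

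One further statement decides how far the matter reaches. Under Primary outcome, on the FEV1 item of the ACQ: "The clinical score of forced expiratory volume (% of predicted, pre-bronchodilator) will be scored on similar scale".

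The legend to Figure 1 places the inflammation measurements in the first visit and pulmonary function in the second. It says that patients are evaluated again after the 24 sessions. No section comments on the difference between the two salbutamol figures.

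**The concern.** The same drug is given by the same route to the same patients, yet one dose is in milligrams and the other in micrograms. The numbers do not compensate for the change of unit, so the gap is one of orders of magnitude.

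Two things are at stake. First, the bronchodilator response is the change in FEV1 after a stated dose. If that dose is in doubt, a reader cannot repeat the measurement from the article. Second, this is an instruction to give a drug, where the unit is part of the instruction. Anyone who worked from the printed figure alone would face a safety question.

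**Working it through.** The plan has no derived figure of its own to reproduce here. The check is a unit conversion, followed by a look at where the dose enters the analysis.

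**Inputs**

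| Quantity | Value as written | Source in the protocol article |
|---|---|---|
| Inhaled salbutamol, spirometry | 200 mg | Pulmonary function |
| Inhaled salbutamol, before hypertonic saline | 400 μg | Airway inflammation |
| Target sample | 48 patients | Sample size |
| Assumed drop-out | 20% | Sample size |

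**Step 1: common unit.** 200 mg × 1,000 μg/mg = 200,000 μg.

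**Step 2: ratio.** 200,000 μg / 400 μg = 500. In milligrams, 200 / 0.4 = 500.

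**Step 3: could text conversion explain it?** A micro sign lost when the PDF was read would produce this kind of discrepancy. However, the sign survives in the Airway inflammation section of the same document, both in the salbutamol dose and in the aerosol particle diameter (4.5 μm). A systematic loss is therefore unlikely. The printed page is not available here, so a single lost character cannot be ruled out.

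**Step 4: where the dose enters the analysis.**

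- ACQ (primary outcome): its FEV1 item is taken before the bronchodilator, so the dose does not enter.
- Sample size: based on a 0.5-point ACQ difference and a standard deviation of 0.72, so the dose does not enter.
- Planned ANOVA and intention-to-treat population: neither depends on the dose.
- Bronchodilator response: measured after the dose, so this is the one quantity directly tied to it.

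**Step 5: how many administrations the sentence could cover.** If post-bronchodilator spirometry is done at both evaluations and nobody drops out, the count is 48 × 2 = 96. If the planned 20% miss the second evaluation, 48 × 0.80 = 38.4, and the total is about 48 + 38 = 86. Repetition at the second evaluation is inferred from the Figure 1 legend. The Abstract's list of before-and-after measurements does not name spirometry.

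**The case against.** The strongest reply is that this is not a contradiction in the strict sense. Bronchodilator-response testing and premedication for sputum induction are different procedures, and nothing in the article says that their doses must match. That stands. The point rests on the change of unit and the order of magnitude, not on the two figures being unequal.

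The reply has further parts:

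- **Main inference.** The dose touches neither the primary outcome nor the sample size. This stands in full.
- **Interpretability.** A reader might infer that the bronchodilator-response results cannot be interpreted. The article does not support that. The 12% and 200 mL rule is fully stated, and if one consistent dose was given, comparisons over time and between groups remain meaningful. Only exact replication from the text is impaired.
- **Safety.** A reader might infer that patients were exposed to the dose as printed. Nothing shows this. Recruitment is from one university hospital clinic, the article condenses a fuller protocol that is not shown, and nothing indicates that the working document carries the same figure. The safety point is conditional on literal use of the text.
- **Extent.** The count of 96 is a ceiling on how often the sentence could apply, not a count of dosing errors.
- **Timing.** Under Study status, the study is described as ongoing with data still being analysed. Whether any evaluations remain is unknown, so advice to assessors may come too late to matter.

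None of this explains the figures as printed. The article also does not merely leave a detail to a longer document: it states a dose and a unit that sit badly with its own other figure.

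**Conclusion.** The point holds as a probable unit error in a written patient procedure. The two stated doses of inhaled salbutamol differ by a factor of exactly 500, with a change of unit and no explanation.

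The consequence is limited. The reproducibility of the bronchodilator-response measurement is impaired, and there is a safety implication only if the text were followed literally. The ACQ comparison and its power are untouched.

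The conclusion assumes that the text available here reproduces the printed units. The survival of the micro sign elsewhere makes this likely but does not prove it. It does not assume that the two procedures should use equal doses, and it takes no position on which figure or unit is right.

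**What to change.** The investigators should reconcile the salbutamol dose and unit under Pulmonary function with those under Airway inflammation and with the procedure actually used. They should then correct the article's text and report the dose given when the bronchodilator response is published. If the two procedures are meant to use different doses, one clause saying so would settle the matter for readers. If evaluations remain, the dose should also be confirmed with the assessors. If none remain, correcting the record is enough.

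The cost is a one-line correction and, where relevant, a short note to the assessors. The design, sample size and analysis do not change.

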### Other notable outcomes – possible mechanisms

#### Hyperventilation syndrome symptoms

Nijmegen questionnaire will be used to assess hyperventilation symptoms. We will compare the differences between the 2 treatments in the absolute change in hyperventilation symptoms post-intervention. The Nijmegen questionnaire is composed of 16 questions that quantify abnormal breathing; (each question range in scale from 0 (never) to 4 (very often)). A total score of ≥23 establishes hyperventilation syndrome with a sensitivity of 91% and a specificity of 95%
[32].

#### Autonomic nervous control

Patient’s heart rate variability (HRV) will be assessed at rest pre and post-intervention by a heart rate monitor (Polar S810i, Finland) as previously described
[33] and data will be recorded and immediately transmitted to the computer for analysis using the Polar Precision Performance software (release 3.00, Kempele, Finland). HRV parameters will be analyzed according to the components of low frequency (LF), high frequency (HF), LF/HF ratio, standard deviation of the differences between adjacent normal RR intervals (RMSSD) after Fourier transformation and noise filtering through the program Kubios HRV Analysis Software version 2.0 (Kuopio, Finland). Data will be recorded in a 5 minutes interval.

#### Thoracoabdominal kinematics

It will be evaluated using optoelectronic plethysmography (OEP System, BTS, Italy), as previously described
[34]. Video is recorded with 8 solid-state charge-coupled cameras operating at 100 frames per second and synchronized with an infrared flashing light-emitting diode. Four cameras will be positioned in front of the subject and four behind. Eighty-nine retro-reflective markers will be placed on the anterior and posterior sides of the trunk according to the protocol previously described
[35]. A three-dimensional calibration of the equipment will be performed, based on the manufacturer’s recommendations. The assessment will be performed with the subject seated on a chair without back support and patients will be requested to perform 8 quiet breaths followed by 8 deep breaths guided by blinded therapist. The average of 6 homogeneous respiratory cycles will be used for the data analysis. The chest wall volumes and inspiratory muscular activity will be assessed concurrently. The following variables will be measured: total chest wall and compartmental volumes; time variables and thoracoabdominal asynchrony; activity of the sternocleidomastoid, and external superior and inferior intercostal muscles by surface electromyography (EMG BTS, Italy).

#### Airway inflammation

It will be quantified in collected sputum samples and exhaled fraction of nitric oxide (FE_NO_). Before the sputum collection, subjects will be advised to blow their nose and rinse their mouth with water and swallow it to reduce contamination of the sputum specimen with postnasal drip and saliva. Then, patients will inhale 400 μg of salbutamol followed by a 3% hypertonic saline solution inhaled over 15 min using an ultrasonic nebulizer with an output of 2.4 mL.min^-1^ and a mass median aerodynamic diameter of 4.5 μm as previously described
[36]. Sputum samples will be visually separated from the saliva and divided into 2 aliquots. One aliquot will be spread over a glass slide, to be fixed and stained with Diff Quick (Sigma-Aldrich, São Paulo, Brazil). The second aliquot will be treated with 0.1% of dithiothreitol (Sigma-Aldrich, USA) and stirred using a vortex mixer for total and differential cell counts. The total cell counts will be performed using a Neubauer chamber, and the cell suspension will be adjusted to 1.0 × 10^6^.mL^-1^. Differential cells counts will be classified as eosinophils, lymphocytes, neutrophils, macrophages, squamous cells, goblet cells, and ciliated cells on the basis of their morphology by a single-blinded investigator.

*FE*_*NO*_ will be measured according to the ATS/ERS guidelines (2011)
[37]. Briefly, patient’s will be asked to blow into a Mylar bag, (keeping the expiratory pressure at the mouth at 12 cm H_2_O to avoid air contamination from the nasal cavity). Exhaled air will be filtrated before being collected into the bag, and the expiratory pressure achieved by the individual will monitored by a manometer. All collected samples will be mixed 10 s before the determination of NO concentration by chemiluminescence (Sievers 280 NOA; Sievers Instruments, USA) and analyzed up to 24 h after sample collection. The equipment will be calibrated before each analysis.

#### Systemic inflammation

It will be quantified in 15 mL of blood sample obtained at rest. Patients will be advised to fast for at least 8 hours not carry out physical activity and not ingest alcoholic and/or caffeinated beverages for 24 hours before the blood collection. Blood samples will be centrifuged at 1800 rpm for 10 minutes at 0°C and will be stored at -70°C. Th1 (IL-6, TNF), Th2 (IL-4, IL-5, and IL-13), and anti-inflammatory (IL-10 e IL-1ra) cytokines as well as osteopontin will be quantified in duplicate by using commercial cytometric bead array kits (BD Biosciences, USA). Serum levels of cortisol will be analyzed by fluoroimmunoassay using the AutoDelfia system (Wallac, Finland).

### Additional measures

To appropriately describe our patients, we will collect basic demographic and medical information including age, smoking status, ethnicity, gender role and anthropometrics (height and weight). It will also be collected self-reported details of current and lifetime history of diagnosis of asthma, other respiratory diseases, cardiovascular disease risk factors, cancers, auto-immune diseases, and all current medications. All reported clinical data will be verified by a hospital medical record review.

### Data analysis

#### Sample size

It was estimated based on a minimal important difference of 0.5 points on the ACQ questionnaire with a standard deviation of 0.72
[38]. A sample size of 40 patients was required for a 5% level of significance with 80% power using a two-tailed *t* test. An estimated drop-out rate of 20% was used to determine the final target sample size of 48 patients.

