## Discussion

Asthma symptoms have a significant impact on patient’s life and the proper clinical treatment is very important to reduce those symptoms; however, sometimes clinical control is difficult, despite the appropriate amount of prescribed medication. Aerobic and breathing exercises have been considered important as complementary therapies in addition to the pharmacological treatment mainly for patients with controlled or partially controlled asthma, because they improve disease control
[1]. In addition, asthmatic patients have 2 main clinical conditions that support the importance of these non-pharmacological interventions: they are more prone to be physically deconditioned compared with their peers and they also have a high prevalence of hyperventilation symptoms
[39]. Because of that, asthmatic patients tend to face more negative attitudes toward exercise and present higher levels of anxiety and depression
[40, 41].

The proposal of our study, comparing the benefits of aerobic and breathing exercises training on clinical control, seems quite relevant because even if both techniques have similar effects in reducing asthma symptoms, we will further investigate some mechanisms in order to understand how patients develop their benefits at each and every intervention. There is evidence that aerobic exercises improve cardiovascular fitness, resistance to stress and health related quality of life (HRQoL) as well as decrease dyspnea, incidence of exercise-induced bronchospasm, use of corticosteroids, inflammatory parameters, anxiety and depression related to asthma
[9]. A recent Cochrane review confirmed these benefits and also demonstrated that physical training can be well tolerated among people with asthma
[42]. These studies show us that there was some evidence to suggest that physical training may have positive effects on HRQoL. Therefore, exercise training can also improve daily living physical activity and reduce dyspnea
[43]. In our opinion, the improvement in aerobic capacity will reduce airway inflammation levels improving clinical control.

In addition, the practice of breathing exercises have been shown to improve HRQoL, peak expiratory flow, asthma symptoms as well as to reduce the levels of hyperventilation symptoms, anxiety and depression and medication consumption

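### The stated 80% power for 40 patients does not follow from the plan's own inputs: if 0.72 is the SD of change, power for the between-arm comparison is about 57%

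*Protocol article*

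**What the plan says.** All references are to the protocol article. Under Sample size, the calculation rests on a "minimal important difference of 0.5 points on the ACQ questionnaire with a standard deviation of 0.72". The conclusion is: "A sample size of 40 patients was required for a 5% level of significance with 80% power", with a two-tailed t test. A 20% drop-out allowance then raises 40 to 48.

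The Methods/design part of the Abstract shows that 48 is the total to be divided between the aerobic and breathing groups, so 40 is also a total.

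Under Primary outcome, the comparison is between arms: "We will compare the differences between the 2 interventions in the absolute change in asthma control post-intervention". The first research question in the Background also asks which of the two interventions is the more effective.

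**The concern.** The sample size section gives every ingredient of a t-test calculation, so its result can be checked, and for two independent arms it does not come out at 40. This is the only justification given for the size of the trial, and it concerns the primary outcome. If the power is well below 80%, a true difference of 0.5 points, which is the plan's own minimal important difference, would be missed far more often than the one time in five that the reader is told to expect. A non-significant result would then carry less information than the protocol implies.

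**Working it through.** **Inputs.** From Sample size: difference 0.5, SD 0.72, two-sided 5%, power 80%, t test, 40 patients, 20% drop-out. From the Abstract: two groups, 48 in total. Assumption: 1:1 allocation, since the article states no ratio; hence 20 per arm.

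**Attempt to reproduce 40 as a between-arm test, with 0.72 as the SD of the analysed change.**
- Standardised difference: d = 0.5/0.72 = 0.694.
- Normal approximation: n per arm = 2 × (1.960 + 0.842)² × 0.72² / 0.5² = 32.6, so 33 per arm, 66 in total.
- Noncentral t: 33.5, so 34 per arm, 68 in total.
- The stated total of 40 is not reproduced.

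**Power at the planned sizes** (noncentral t, noncentrality d × √(n/2)):

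| Per arm | Meaning | Power |
|---|---|---|
| 19 | 48 less 20% drop-out (about 38) | 54.9% |
| 20 | the stated 40 | 57.2% |
| 24 | all 48 analysed | 65.4% |

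At 20 per arm the noncentrality is 0.694 × √10 = 2.20, against a critical value of 2.024 on 38 degrees of freedom. The normal approximation gives 59.3%.

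**What 20 per arm would support at 80% power.** The detectable standardised difference is 0.909. With SD 0.72 that is 0.909 × 0.72 = 0.65 points. Alternatively, to detect 0.5 points the SD of change would have to be 0.5/0.909 = 0.55.

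**Other readings of the stated figure.**
- One-sided test: 26.3, so 27 per arm, 54 in total. This is not 40, and the article says two-tailed.
- 40 per arm: power 86.6%, which is not 80% and conflicts with 48 as the total.
- Paired or one-sample t test within one arm: 18.3, so 19 per arm, 38 in total (83.8% power at 20). This is close to 40 but not equal to it.

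**If 0.72 is the SD of a single score.** The SD of change is then 0.72 × √(2(1 − r)), where r is the pre-post correlation. The article does not give r, so this is a range over assumed values:

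| r | SD of change | Power at 20 per arm |
|---|---|---|
| 0.3 | 0.85 | 44% |
| 0.5 | 0.72 | 57% |
| 0.7 | 0.56 | 79% |

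Setting the SD of change to 0.55 gives 2(1 − r) = (0.55/0.72)² = 0.58, so r is about 0.71. That is the correlation needed for 80%.

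**The case against.** The best defence is that the article does not say what kind of SD 0.72 is. If it is the SD of a single score and the pre-post correlation is about 0.71, a between-arm test does need about 20 per arm and the stated figure would be right. This stands as a possibility, and it is why the 57% must be given as conditional. It does not rescue the statement as written: the correlation is not among the plan's inputs, and the same reading gives 44% at 0.3 and 57% at 0.5.

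The planned repeated-measures ANOVA (Proposed statistical analyses) does not help either. With two time points, its group-by-time test is equivalent to the t test on change scores.

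A reader might draw two stronger conclusions that the document does not support.
- **That the trial was sized for each arm's own pre-post change.** The within-arm calculation comes near, at 38, and is one possible origin. But the article mentions no paired test, and a between-arm calculation with an unstated correlation of about 0.71 fits 40 at least as well. The origin cannot be settled from the text.
- **That a null result is headed for an equivalence claim, so an equivalence rule should be added.** The Discussion says "even if both techniques have similar effects in reducing asthma symptoms", but conditionally, to motivate the study of mechanisms; no equivalence claim is planned. The Primary outcome section uses 0.5 as a threshold for a clinically effective treatment, not as a between-arm margin. At 20 per arm and SD 0.72 the expected half-width of the 95% interval is 2.024 × 0.72 × √(2/20) = 0.46, so an interval of that width would lie inside ±0.5 only if the observed difference were below about 0.04.

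**Conclusion.** The point holds: 80% power with 40 patients does not follow from the stated difference, SD, significance level and test for the comparison named as primary. The gap between 40 and 68 is too large for rounding or software to explain. If 0.72 is the SD of change, and allocation is 1:1, power is about 57% with 20 evaluable patients per arm, so a true 0.5-point difference would be missed about 43% of the time (1 − 0.57). Even with all 48 analysed, power is 65%.

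If 0.72 is a single-score SD, the true power depends on an unstated correlation and could be lower or close to 80%. The finding is therefore that the 80% claim is unsupported as written, not that the power is known to be 57% under every reading.

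**What to change.** In the Sample size section:
1. Delete the 80% power claim for 40 patients.
2. State whether 0.72 is the SD of the change in ACQ or of a single score and, if the latter, the assumed pre-post correlation.
3. Restate the power accordingly. If 0.72 is the SD of change, suitable wording is: *With 20 evaluable patients per arm, power to detect a 0.5-point between-arm difference in change is 57%; the difference detectable with 80% power is 0.65 points.*
4. State that the primary result will be reported as the between-arm difference in change with its 95% confidence interval, so that readers can see what the data exclude.

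This changes wording and reporting only. It needs no extra patients and no equivalence margin. Study status says the study is ongoing and data are still being analysed, so a new decision rule at this point would be a late change to the analysis; correcting the power statement is not. The one cost is a less favourable stated power.

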**Methods/design:**

This is a prospective, comparative, blinded, and randomized clinical trial with 2 groups that will receive distinct interventions. Forty-eight asthmatic adults with optimized medical treatment will be randomly divided into either aerobic (AG) or breathing exercises (BG). Patients will perform breathing or aerobic exercise twice a week for 3 months, totalizing 24 sessions of 40 minutes each. Before intervention, both groups will complete an educational program consisting of 2 educational classes. Before and after interventions, the following parameters will be quantified: clinical control (main outcome), health related quality of life, levels of anxiety and depression, daily living physical activity and maximal exercise capacity (secondary outcome). Hyperventilation syndrome symptoms, autonomic nervous imbalance, thoracoabdominal kinematics, inflammatory cells in the sputum, fraction of exhaled nitric oxide (FE_NO_) and systemic inflammatory cytokines will also be evaluated as possible mechanisms to explain the benefits of both interventions.

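### Minor arithmetic error: the 20% drop-out allowance multiplies 40 by 1.2, so 48 randomised leave about 38 patients with post-intervention data at that rate, not 40

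*Protocol article*

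**What the plan says.** The Sample size section, under Data analysis in the protocol article, gives the whole chain in three sentences. The inputs are a "minimal important difference of 0.5 points on the ACQ questionnaire with a standard deviation of 0.72". From these it concludes: "A sample size of 40 patients was required for a 5% level of significance with 80% power using a two-tailed" t test. It then allows for losses: "An estimated drop-out rate of 20% was used to determine the final target sample size of 48 patients".

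The abstract (Methods/design) shows that 48 is the total over both groups: "Forty-eight asthmatic adults with optimized medical treatment will be randomly divided into either aerobic (AG) or breathing exercises (BG").

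No formula is given for the step from 40 to 48. The section on analysis populations and missing data says that the main analyses follow intention-to-treat and keep every randomised patient, including those who do not complete the post-intervention assessments. The article names no method for handling their missing values.

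**The concern.** A drop-out allowance exists so that the required number remains after the expected loss. The loss is a share of those randomised, so the required number has to be divided by the share retained. Adding 20% to the required number gives too small a target, because the 20% is later lost from the larger figure.

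At stake is whether the target does what its sentence sets out to do. At the plan's own drop-out rate, the number of patients with a post-intervention Asthma Control Questionnaire (ACQ) score falls below the number that the plan calls required for its primary comparison.

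**Working it through.** **Inputs**, all from the Sample size section: 40 required in total; drop-out 20%; target 48; difference 0.5 ACQ points; SD 0.72; two-sided 5%; power 80%. The abstract confirms that 48 covers both groups. The allocation ratio is not stated. I assume 1:1, which affects the power figures but not the drop-out arithmetic.

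**Step 1. Reproduce the plan's figure.** 40 × (1 + 0.20) = 48, an exact match. Nothing else in the article accounts for 48.

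**Step 2. The number that meets the purpose.** 40 / (1 − 0.20) = 50, or 25 per arm.

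**Step 3. What 48 delivers.**
- At 20% loss: 48 × 0.80 = 38.4, so about 38, or 19 per arm.
- Largest loss that still leaves 40: 1 − 40/48 = 16.7%, which is 8 patients of 48.

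**Step 4. Cost of this step alone.** Take at face value that 20 per arm gives 80% power for a difference of 0.5. In a two-sided two-sample t test that implies an SD of about 0.55. With that SD, 19 per arm gives about 77.8%. The drop-out step therefore costs 80 − 77.8 = 2.2 points.

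**Step 5. Power with the printed inputs.** The standardised difference is 0.5/0.72 = 0.694. In a two-sample t test with n per arm, the noncentrality is 0.694 × √(n/2).

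| Total with data | Per arm | Noncentrality | Power |
|---|---|---|---|
| 38 | 19 | 2.14 | 54.9% |
| 40 | 20 | 2.20 | 57.2% |
| 48 | 24 | 2.41 | 65.4% |
| 50 | 25 | 2.46 | 67.2% |
| 68 | 34 | 2.86 | 80.5% |

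Moving from 40 to 38 again costs about two points (57.2 − 54.9 = 2.3). The distance from 57% to the stated 80% is already there at 40, before any drop-out. By normal approximation, n per arm = 2 × (1.96 + 0.84)² × (0.72/0.5)² ≈ 32.5, so 33 per arm (66 in total). The t test needs 34 per arm (68 in total).

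**Step 6. Does the error carry forward?** If the base were corrected to 68, multiplying would give 68 × 1.2 = 81.6, so 82. Dividing gives 68/0.8 = 85, or 86 for equal arms. The method of inflation matters whatever base is used.

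**The case against.** **It is only two patients and the 20% is a guess.** This stands as to weight. The rate is described as an estimate, and 16.7% is well within the uncertainty of such an estimate. No analysis or conclusion depends on the difference between 48 and 50.

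**No formula is stated, so nothing is contradicted.** A reader might infer that the three printed figures cannot all be true. That goes too far. The section does not say in so many words that 40 will remain after 20% of those randomised are lost, and the figures agree with each other under the familiar shortcut of adding 20%. What stands is that the shortcut falls short of the purpose of a drop-out allowance. If a loss of eight patients was meant, the rate is 8/48 = 16.7% and the printed 20% is the figure to correct.

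**Intention-to-treat keeps all 48.** This is a fair qualification: the nominal analysis set is 48, not 38. But a patient without a post-intervention ACQ adds little to a comparison of change, and the article gives no imputation. The plan also inflates for drop-out, which treats drop-outs as lost information.

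**The larger fault is the 40.** This is correct. A reader might take the 57% and 55% as the damage done by the drop-out step, or conclude that randomising 50 would restore 80% power. Neither follows: 50 randomised with 20% lost returns to 40 with data, at about 57% on the printed inputs.

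**Conclusion.** The point holds as a minor error. The target of 48 comes from multiplying by 1.2. At the stated 20% drop-out it leaves about 38 patients with post-intervention data, not 40; it covers 16.7%, and 20% would need 50. Taken alone, this costs about two points of power, from 80% to about 77.8%, on the premise that 40 gives 80%.

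The drop-out arithmetic needs no outside assumption beyond reading the rate as a share of those randomised. The power figures assume 1:1 allocation, a two-sided between-group t test, and 0.72 as the SD of the quantity compared; the section does not say what that SD refers to.

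The documents do not support the stronger conclusion that the drop-out step leaves the trial materially underpowered or forces more enrolment. The shortfall from 80% to about 57% is a separate fault in deriving the 40. It matters here because any corrected sentence would sit next to the 80% claim.

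**What to change.** In the Sample size section, replace the drop-out sentence with wording such as: *48 randomised patients give 40 with post-intervention data at 16.7% drop-out and about 38 at 20%.* Enrolment need not change. Only if both the 20% allowance and the 40 are to be kept must the target read 50.

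In the same edit, correct the power statement. Either report the power that the printed inputs give (about 57% at 20 per arm, 55% at 19 per arm, under the assumptions above), or state the design and SD under which 40 does give 80%. Adding the figure for 19 per arm while leaving 80% for 40 in place would create a new contradiction. The text should make clear that this larger gap comes from the 40 and not from the drop-out allowance.

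It would also help to add a clause noting that the main analyses keep all randomised patients, so that 38 is read as the number with post-intervention data and not as the size of the analysis set.

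The cost is a few sentences of text. The Study status section says the trial is ongoing with data being analysed, so the gain is an accurate statement of what the trial can detect and not a change in its conduct.
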